### Sample Analysis

Exosomes will be isolated using a well-established commercial kit and will be characterized using exosome markers. The tumor markers will be analyzed by transmission electronic microscopy, reverse transcription-quantitative polymerase chain reaction (RT-qPCR), and flow cytometry. Transmission electronic microscopy is typically used to characterize exosomal markers. RT-qPCR is a well-established tool for detecting gene expression and is frequently used in exosome analysis. However, conventional flow cytometry may be inconvenient for exosome analysis given the small size of exosomes. Therefore, we will use aldehyde/sulfate latex beads to capture the exosome. This technique was recently proposed to advance conventional flow cytometry as a suitable tool for analyzing exosomal markers [7].

### Data Collection

Data collected during the study will be recorded on a case report form for patients and control subjects. On the initial visit, age, sex, and medical history will be noted. For patients, date of disease diagnosis, surgical procedures, and pathological results will be noted.

### Sample Size and Statistical Analysis

A selected group of 60 patients with renal cancer and 40 control subjects will be included in the study (Figure 1). The aim of this project is to evaluate the feasibility of detecting tumor exosomes as a liquid biopsy for CCRCC. We assume a 90% assay feasibility rate, 5% unilateral α, 90% power, and 10% patient withdrawal before the initial assay. According to the one-step Fleming design, 60 patients are required. The assays of the 60 patients will be compared with those of controls to evaluate if the tumor exosomes could be cancer markers.

The diagnostic performance of tumor exosomes will be evaluated by receiver operating characteristic curves. The area under the curve will be determined with its 95% CI. Analyses will be performed using SAS 9.4.

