**Conclusions:**

We expect to demonstrate that urinary tumor exosomes could be a novel liquid biopsy to diagnose CCRCC and to guide clinicians in treatment decision-making.

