## Introduction

Renal cell carcinomas are serious and common cancers [1]. Approximately 70%-80% of kidney cancers are clear cell renal cell carcinomas (CCRCCs). Patient management is based on imaging (abdominal ultrasound and scanner), surgical excision of the tumor, and pathological analysis. Approximately one-third of patients with CCRCC have a locally advanced or metastatic tumor at the time of diagnosis and nearly 30% of treated patients will develop secondary metastases [1]. Recent advances in imaging techniques have increased the detection of kidney tumors; however, not all tumors are cancerous, with 10%-15% of all kidney tumors being benign and 20%-30% of tumors smaller than 4 cm being benign [2]. A tissue biopsy is therefore necessary to confirm the diagnosis and avoid unnecessary nephrectomy. For metastatic cancers, tissue biopsy is also essential for establishing the targeted therapy. This biopsy of tumor material is invasive and painful. Alternative techniques such as liquid biopsy would help reduce the rate of tissue biopsy. Therefore, development of a simple biological test for diagnosis is essential.

The notion of liquid biopsy has been mentioned in recent publications [3]. Liquid biopsies are based on the detection of cancerous biomarkers in body fluids, mostly in the blood, but can also include the urine, saliva, or other fluid. Liquid biopsies are preferable to tissue biopsies because they are less invasive.

Exosomes are small nanoparticles that are secreted into the extracellular medium by different cell types [4,5]. We propose detecting urinary exosomes from patients with CCRCC. A urine sample would be preferable to a blood sample because of the anatomical proximity of the urine to the kidney tumor. Moreover, urine is the simplest biofluid that can be obtained. We and others have found that urine is an important target for the exploration of markers for renal diseases [6]. The tumor exosomes from CCRCC in the urine are particularly abundant because of the location of the tumor directly in contact with the urine. Our hypothesis is that tumor exosomes present in the urine of patients with CCRCC could be detected. Our aim is to develop a reliable technique for the detection of tumor exosomes in the urine of patients with CCRCC to explore their usefulness as a liquid biopsy of CCRCC.

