### Study Population

There is no available publication in the literature to calculate the number of subjects required for this type of study. Thirty patients receive surgery for removal of CCRCC in our department per year. Therefore, we propose to study 60 patients over 2 years. In addition, 20 control patients without cancer in our department are expected per year. Therefore, we propose studying 40 controls over 2 years. Eligibility criteria for cancer patients and controls are listed in Textbox 1. The age of the control group will be determined in agreement with the average age of occurrence of the CCRCC patients included in the study.

Inclusion and exclusion criteria of participants.

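### The AUC and cutoff rest on controls not selected for a renal mass, so they cannot answer the benign-versus-malignant question that motivates the test

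*Protocol article*

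**What the plan says.** The Introduction sets the clinical problem among people who already have a renal mass. It cites "10%-15% of all kidney tumors being benign and 20%-30% of tumors smaller than 4 cm being benign", concludes "A tissue biopsy is therefore necessary to confirm the diagnosis and avoid unnecessary nephrectomy", and adds "Alternative techniques such as liquid biopsy would help reduce the rate of tissue biopsy". The Abstract's Conclusions expect to show that "urinary tumor exosomes could be a novel liquid biopsy to diagnose CCRCC and to guide clinicians in treatment decision-making".

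The comparisons are set elsewhere:

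- Sample Size and Statistical Analysis: "The assays of the 60 patients will be compared with those of controls to evaluate if the tumor exosomes could be cancer markers". The same section evaluates diagnostic performance by ROC curves and gives the AUC with a 95% CI.
- Study Objectives and Endpoints: all three secondary endpoints compare CCRCC patients with controls.
- Inclusion criteria for controls: adults hospitalised in urology with no known cancer. A renal mass is not required.
- Study Population: the one stated alignment of controls to cases is on age, "The age of the control group will be determined in agreement with the average age of occurrence of the CCRCC patients included in the study".
- Discussion: a cutoff for cancer detection will be determined, announced straight after the expected contrast with control subjects.

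Two further points bear on the remedy. The inclusion criteria for patients admit any renal mass scheduled for surgery, and Data Collection records the pathology result.

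**The concern.** The patients in whom a liquid biopsy could replace a tissue biopsy are those with a renal mass of unknown nature. The results that matter for them are how the marker behaves in CCRCC and how it behaves in benign or non-clear-cell masses. No stated analysis compares these groups. The controls represent a different population, so specificity, AUC and cutoff are all estimated in people to whom the biopsy question does not apply.

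This is separate from whether cases are labelled correctly. Even if every case is a confirmed CCRCC, the comparison still does not estimate discrimination among masses. At stake is how the result is read: a high AUC reported as diagnostic performance, together with a cutoff, could be taken as support for reducing biopsy and could shape the multicentre study that the Discussion envisages.

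**Working it through.** **1. What the stated 60 is sized for.** Inputs (Sample Size and Statistical Analysis): feasibility rate 0.90, one-sided α 0.05, power 0.90, 10% withdrawal. The null rate p0 is not given in the article, so it is assumed here. The one-stage normal approximation is n = [(1.645√(p0(1−p0)) + 1.2816√(0.9×0.1)) / (0.9−p0)]².

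- p0 = 0.75: (0.7123 + 0.3845)/0.15 = 7.312; squared 53.5, so 54; 54/0.9 = 60.
- p0 = 0.70 gives 33, or 37 after withdrawal. p0 = 0.80 gives 109, or 122.

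The 60 is reproduced with p0 = 0.75. It sizes assay feasibility, not any AUC, so the point below does not depend on it.

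**2. Does the AUC against controls determine the AUC among masses?** Illustration, by assumption: normal marker with equal variance, perfect labels, CCRCC mean d above controls, and non-CCRCC masses a fraction f of the way from control to CCRCC level. Then AUC against controls = Φ(d/√2), AUC against masses = Φ(d(1−f)/√2), and the specificity in masses of a cutoff with 90% specificity in controls = Φ(1.2816 − f·d). With d = 1.81 the AUC against controls is 0.90.

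| f | AUC against other masses | Specificity in those masses |
|---|---|---|
| 0 | 0.90 | 0.90 |
| 0.25 | 0.83 | 0.80 |
| 0.50 | 0.74 | 0.65 |
| 0.75 | 0.63 | 0.47 |
| 1 | 0.50 | 0.30 |

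The documents give no value for f. Correct labelling does not narrow the range.

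**3. What 60 unselected masses would contain.** Inputs (Introduction): benign share b = 10%-15% of tumours; clear cell share c = 70%-80% of kidney cancers. Assumptions: the 60 are unselected masses, and these rates hold for operated masses.

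| b, c | CCRCC = 60(1−b)c | Benign = 60b | Other cancers = 60(1−b)(1−c) | All non-CCRCC |
|---|---|---|---|---|
| 0.10, 0.80 | 43.2 | 6 | 10.8 | 16.8 |
| 0.10, 0.70 | 37.8 | 6 | 16.2 | 22.2 |
| 0.15, 0.80 | 40.8 | 9 | 10.2 | 19.2 |
| 0.15, 0.70 | 35.7 | 9 | 15.3 | 24.3 |

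So there are about 36-43 CCRCC and 17-24 non-CCRCC masses. At the two extremes of that range, other cancers make up 10.8/16.8 = 64% and 15.3/24.3 = 63% of the non-CCRCC masses.

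**4. Precision.** Hanley-McNeil, m cases and n comparators: SE² = [A(1−A) + (m−1)(R1−A²) + (n−1)(R2−A²)]/(mn), with R1 = A/(2−A) and R2 = 2A²/(1+A). A = 0.80 is assumed, giving R1−A² = 0.02667 and R2−A² = 0.07111. For 43 v 17: (0.16 + 42×0.02667 + 16×0.07111)/731 = 0.00331; SE 0.0575; ×1.96 = 0.113.

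| Comparison | m v n | 95% half-width |
|---|---|---|
| All 60 v controls | 60 v 40 | 0.085 |
| CCRCC v controls | 43 v 40; 36 v 40 | 0.095; 0.102 |
| CCRCC v non-CCRCC masses | 43 v 17; 36 v 24 | 0.113; 0.110 |
| CCRCC v benign masses | 43 v 6; 36 v 9 | 0.156; 0.140 |

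The like-for-like contrast is 0.11 against 0.095-0.10. The 0.085 would count all 60 masses as CCRCC.

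**5. If the 60 are instead confirmed CCRCC.** Reaching 60 from unselected masses takes 60/(0.90×0.80) = 83 to 60/(0.85×0.70) = 101 masses, hence 23-41 non-CCRCC masses. Half-widths are then 0.096 (60 v 23) to 0.085 (60 v 41), but only if those samples are kept and assayed.

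**The case against.** The strongest reply is that this is a descriptive pilot whose objective is detection and feasibility. Comparing cases with non-cancer controls before a harder comparator is a defensible first step. The article asks only whether exosomes could be cancer markers, places therapeutic guidance in the future, and makes a multicentre study conditional on success. An analysis by histology may also stand in the full protocol or analysis plan, which are not shown. All of this stands as far as the detection aim goes. It does not cover the AUC presented as diagnostic performance or the cutoff: the article names their comparator, and that comparator does not match the problem it describes.

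Three stronger readings are tempting but not supported:

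- A reader might infer that the article commits the test to deciding which masses are biopsied or removed. It does not. That use is a fair reading of the background, not a stated objective.
- A reader might infer that the right comparator is already enrolled at no added cost. The inclusion criteria admit any renal mass, but the Abstract's Methods and Study Population describe the 60 as CCRCC patients. If they are, the 60 contain no other masses, and whether others are kept is not stated.
- A reader might infer that an AUC against all non-CCRCC masses would support a claim about avoiding nephrectomy. At the extremes in step 3, about 63%-64% of those negatives would themselves be cancers, so it would not.

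The benign share among masses already scheduled for surgery may also differ from the Introduction's rates. The documents do not give it.

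**Conclusion.** The point holds for the ROC analysis, the cutoff and any diagnostic conclusion, not for the pilot's detection and feasibility aim. As written, the plan can show that the marker differs between CCRCC and urology inpatients without known cancer. It cannot show discrimination among renal masses, and under the binormal illustration an AUC of 0.90 against controls leaves the within-mass AUC anywhere from 0.90 to 0.50.

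A within-mass comparison is feasible but imprecise: a half-width of about 0.11 against all non-CCRCC masses and 0.14-0.16 against benign masses alone. These figures assume an AUC of 0.80, 60 unselected masses, and the Introduction's rates among operated masses. The change should be made, but its absence does not invalidate the pilot.

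**What to change.** - Keep and assay the sample from every renal mass admitted under the inclusion criteria, whatever its pathology, and state whether the 60 counts masses or confirmed CCRCC.
- Add a secondary, exploratory ROC curve and AUC with 95% CI for the CD63+/CA9+ result in pathology-confirmed CCRCC against enrolled non-CCRCC masses. Report benign and non-clear-cell masses separately as well.
- Label the AUC and cutoff against the 40 controls as proof of concept.
- State that no claim about reducing biopsy or avoiding nephrectomy will be drawn from the control comparison. Such a claim needs the within-mass results, in particular CCRCC against benign masses, which this pilot can estimate only imprecisely.

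The cost is one more analysis with a wide interval and a more modest conclusion. If the 60 are confirmed CCRCC, there is also the assay work on the other masses (about 23-41 on the Introduction's rates).

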### Patient and Public Involvement

The ethics committee examined the information notice that will be given to participants of this project. This consultation helped to improve the patient information notice on the design and aim of the study so that the participants will clearly understand and decide whether to participate in this study, in agreement with the principle of informed consent.

## Results

This study is currently underway with funding support from the CHU Saint-Etienne of France. Recruitment of all patients will be completed in 2 years. The results of the study will then be communicated via presentations and publications.

## Discussion

Research on liquid biopsy has become a hot topic. Liquid biopsy allows for the detection of tumor markers in bodily fluids for the management of cancer patients. Compared with tissue biopsy, liquid biopsy is noninvasive. Liquid biopsy usually utilizes circulating tumor cells, cell-free DNA, and exosomes. Compared with circulating tumor cells and cell-free DNA, the use of exosomes is relatively more recent, but has shown rapid development. Exosomes carry tumor markers such as nucleic acids, proteins, and lipids, including mRNAs, microRNAs, and signaling molecules that reflect the physiological and pathological condition of the cells of origin [4]. The bilayer lipid membrane of the exosome considerably improves the stability of the internal components; exosomes are therefore a rich source of biomarkers. Exosomes have recently been the subject of research into biomarkers, which hold great promise for cancers [7]. Significant advances in exosome research have been made in body fluids such as saliva, serum, urine, and amniotic fluid [5]. Blood is particularly interesting as a source of liquid biopsy since it contains cancer-specific markers in extracellular vesicles. Currently, most of the research in this field focuses on blood exosomes. Urinary exosomes are also an excellent resource for biomarkers and a promising noninvasive diagnostic instrument for kidney disease [8-11]. Moreover, urine is the easiest available bodily fluid.

Our previous study demonstrated that CA9 is a powerful marker for the diagnosis of CCRCC [12]. Exosomes from the renal tumor could be discharged into the urine since urine is in close contact with the tumor. Thus, we suggest that urinary exosomal CA9 could be used as a biomarker in the diagnosis of CCRCCs. For this purpose, we have designed a pilot study, named PEP-C, to demonstrate whether it is possible to detect exosomal CA9 in the urine of patients with CCRCC. We expect that exosomal CA9 will be detectable in the urine of patients suffering from CCRCCs when compared with that of control subjects. A cutoff corresponding to cancer detection will be determined. Moreover, we will test urinary exosomal VEGFR2 expression since VEGFR2 was found to be highly expressed in CCRCCs [13]. The exosome markers CD9, CD63, and CD81 will also be analyzed as references. These markers will be assessed using transmission electron microscopy, flow cytometry, and RT-qPCR techniques [14,15]. Our aim is to develop a liquid biopsy assay for the diagnosis of CCRCC. In the future, we hope to demonstrate that urinary exosomes could be a powerful tool to diagnose cancer and to guide clinicians in therapeutic decision-making.

Several techniques for the isolation of urinary exosomes have been proposed, which can be classified according to the biochemical principle of purification: ultracentrifugation, filtration, immunocapture, or precipitation [16,17]. Ultracentrifugation isolation is the standard technique for obtaining exosomes. However, ultracentrifuges are not routinely available in clinical laboratories and this method requires a relatively long preparation time. Manufacturers have developed reagents for isolating exosomes from large volumes of urine, such as ExoQuick-TC (System Biosciences). This type of process makes clinical application possible. In preliminary tests for this project, we observed the urinary exosomes by transmission electron microscopy (Figure 2). Typical cup-shaped exosomes were observed. The size and the morphology are two important indicators for defining the urinary exosomes. Our preliminary results showed that urinary exosomes were abundant from cancer patients.
Research on liquid biopsies using urine for CCRCC is very new. To our knowledge, there is almost no publication in this area. In contrast, prostate cancer–specific genes have been detected in urinary exosomes, constituting a new liquid biopsy tool to diagnose high-risk prostate cancer [18,19]. This technique of urine liquid biopsy was developed exclusively for prostate cancer and no such diagnostic method is available for CCRCC at present.

**Figure 2 figure2:**
[figure not shown]
Transmission electron microscopy observation of urinary exosomes.

In conclusion, this will be the first study to evaluate the technical feasibility of detecting urinary exosomal CA9 in CCRCC patients. The results of this study might highlight the strong potential of liquid biopsy through urinary exosomes in the diagnosis of CCRCC. Therefore, if this pilot study is successful, a multicenter study will be envisaged.

## Appendix

Multimedia Appendix 1 External peer report A from CHU St-Etienne.

Multimedia Appendix 2 External peer report B from CHU St-Etienne.

Multimedia Appendix 3 External peer report C from CHU St-Etienne.

## Abbreviations

CCRCC: clear cell renal cell carcinoma
RT-qPCR: reverse transcription-quantitative polymerase chain reaction
VEGFR2: vascular endothelial growth factor receptor 2
